## 2. Methods

### 2.1. Study Design

This study is a prospective, multi-center, single-arm, non-controlled 3-month pilot trial conducted across several European locations including Bulgaria, Germany, Italy, Netherlands, Portugal, and Spain. It is designed as a preliminary three-month intervention (pre-post design) to test the feasibility and effectiveness of a mobile health application, with the goal of laying the foundation for a future 12-month longitudinal study with an intervention group (app) and a control group (standard recommendations). The current study design will be consistent across countries, with minor adaptations to account for local contexts. NCT07011368 is the registration number for this study on ClinicalTrials.gov (https://clinicaltrials.gov/study/NCT07011368 (accessed on 8 July 2025)).

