### 2.6. Follow-Up and Data Collection

The study spans 90 days (3 months) and is structured into five phases: enrollment (Dx), baseline visit (Day 0), and final visit (Day 90) in most of the participating partners. Data collection occurs at baseline and final visits, with regular check-ins via phone calls, or in-person meetings to maintain engagement. Figure 1 summarizes the timeline and interventions at each stage. Each study phase (outlined in Table 4) is described as follows:Enrollment visit (Dx): Informed consent (after receiving written and verbal information about the study’s objectives, risks, and benefits), eligibility assessment (assessed based on anthropometric measurements, and screening questionnaires on general health and lifestyle), and meeting inclusion criteria.Baseline visit (Day 0): Anthropometric data, baseline questionnaires, biological samples (blood, urine, and saliva, where applicable), and instructions on using the HLRS platform. Recommendations will be adapted to the previously diagnosed health status, A1c levels or blood pressure of the participant. Participants will receive instructions on using the HLRS platform.Final visit (Day 90): Repeat assessments and questionnaires to evaluate changes over the study.

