Questionnaires: Validated questionnaires will be via REDCap [26], and include the following:24hR (24-Hour Recall): Completed three times to assess dietary intake [27].BFI-10 (Big Five Inventory—10 Items): A personality assessment tool [28].IPAQ-S (International Physical Activity Questionnaire—Short Form): Measures physical activity levels [29].PHQ-9 (Patient Health Questionnaire—9): Evaluates symptoms of depression [30].PSQI (Pittsburgh Sleep Quality Index): Assesses sleep quality and disturbances [31].UEQ (User Experience Questionnaire): Measures user experience with digital platforms or interventions [32,33].WHOQOL (World Health Organization Quality of Life): Assesses quality of life across different domains [34].FFQ (Food Frequency Questionnaire) of 143 items: Evaluates dietary intake over a specified period [35,36,37,38].

All questionnaire data within REDCap will be securely stored on the Luxembourg Institute of Health (LIH) Cloud, with access controlled by LIH’s IT Department. Wearable device data (from Samsung or Garmin smartwatches) and GameBus information will be stored on the GameBus server, managed by the University of Eindhoven, Netherlands. Nutrida data will be stored on a secure EU-based server provided by NIUM (Amazon). Data from the HDT and calendar application will be housed on a server managed by the Luxembourg Institute of Science and Technology (LIST). Garmin smartwatches will store data directly on the device and smartphone, while Samsung data will not be stored on external company servers outside Europe or on University of Eindhoven servers. Calendar event data is securely stored on servers at LIST, Luxembourg.

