## 3. Statistics

Sample Size Calculation: The study hypothesizes that the use of HLRS (≥45 min per week) will not decrease by more than 20% over the 3-month intervention period. Assuming a 30% standard deviation in usage, a 0.05 significance level, and 80% power, 20 participants would be required for a paired design. To compensate for an expected 33% attrition, 30 participants will be recruited, ensuring sufficient power. An equal distribution of males and females will be targeted to enhance the generalizability of the findings.

Handling of Missing Data and Dropout: No imputation will be performed for missing data. Participants who withdraw will be excluded from further analysis beyond their last available data. In order to maintain sample size and statistical power, replacements will be made as necessary, ensuring at least 20 participants complete the study. This method safeguards the integrity of the data and minimizes potential bias.

Data Analysis: Normality of the data will be assessed through Q-Q plots and Kolmogorov–Smirnov tests. Non-normally distributed data will be analyzed using non-parametric methods such as the Friedman test, followed by pairwise comparisons, and log transformations if appropriate. A significant level of *p* < 0.05 will be considered. Data will be analyzed using SPSS (version 25.0) and R (version 4.4.1). Since outcomes will be mainly descriptive, simple and descriptive statistics will summarize baseline participant characteristics, and changes over time will be assessed using paired t-tests, to evaluate the impact of the intervention on health outcomes.

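### For outcomes measured only at the baseline and final visits, the one non-parametric test named (Friedman with pairwise comparisons) reduces to the sign test; a paired two-occasion rank test should be named

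*Protocol article*

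**What the plan says.** Section 3 (Statistics, Data Analysis) gives the rule for data that fail the normality check: "Non-normally distributed data will be analyzed using non-parametric methods such as the Friedman test, followed by pairwise comparisons"; the sentence goes on to allow a log transformation where suitable. No other non-parametric test is named. The same paragraph assesses change over time with paired t-tests, checks normality of the data without saying whether that means raw values or within-person changes, sets significance at p < 0.05, and calls the outcomes mainly descriptive.

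The schedule is a two-occasion one for most measures. Section 2.1: "It is designed as a preliminary three-month intervention (pre-post design) to test the feasibility and effectiveness of a mobile health application". Section 2.6: "Data collection occurs at baseline and final visits, with regular check-ins via phone calls, or in-person meetings to maintain engagement". The final visit in that section is described as "Repeat assessments and questionnaires to evaluate changes over the study".

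Some measures are not confined to two occasions. The 24 h recall is "Completed three times to assess dietary intake" (section 2.7), without a statement of how the three are spread over the study. The primary outcomes in section 2.7 rest on app use and wearable data, which accumulate between the visits.

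**The concern.** The Friedman test followed by pairwise comparisons is a procedure for three or more repeated measurements. In a pre-post comparison there is a single pair of occasions, so the follow-up step is empty and the overall test keeps only the sign of each change. The two branches of one paragraph therefore assume different designs: the parametric branch assumes two occasions, the non-parametric one at least three.

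The outcomes most likely to fail a normality check are biomarkers, and these come from few people. By Tables 1 and 4, cytokines and oxidative-stress markers are measured at IDISBA only (20 completers required), and glucose metabolism and lipids at UC, UEV and IDISBA (15 + 15 + 20 = 50). In sets of that size, discarding the magnitude of change can cost appreciable power, and the sign test yields no estimate of how large the change was.

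**Working it through.** **1. The plan's own sample size, as a reference case.** Inputs from section 3: change 20%, SD 30%, alpha 0.05, power 80%, paired design. Standardized change d = 20/30 = 0.667. The two-sided normal approximation gives (1.5 × (1.960 + 0.842))² = 17.66, so 18. The exact two-sided paired t-test gives n = 20 with power 80.7%. The stated 20 is reproduced, and 20/(1 − 0.33) = 29.9 gives the stated 30 recruited. I use n = 20 and d = 0.667 below only as a convenient reference; the article gives no effect size for the secondary outcomes.

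**2. Friedman with two occasions.** Each person's two values are ranked 1 and 2. With S increases among n people and no ties, the statistic becomes Q = (2S − n)²/n on 1 degree of freedom, which is the uncorrected sign-test chi-square. At n = 20:
- S = 14: Q = (28 − 20)²/20 = 3.2, below the 5% limit of 3.84.
- S = 15: Q = (30 − 20)²/20 = 5.0, above it.

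So the test rejects when at least 15 of 20 people move the same way. The exact sign test rejects in the same cases; the true size is 4.1%. The two rejection regions also coincide at n = 15, 25 and 52.

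**3. Power for normal changes.** The probability that a person increases is Φ(0.667) = 0.7475. The probability of at least 15 increases in 20 (the opposite tail is negligible) is 60.7%; simulation gives 60.4%. The exact Wilcoxon signed-rank test has 78.4%.

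**4. Other shapes.** n = 20, d = 0.667, two-sided 0.05, changes scaled to unit SD, 40,000 simulations each. The shapes are assumptions; the article gives none.

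| Shape of the within-person change | Wilcoxon | Friedman = sign | Loss (points, rounded) |
|---|---|---|---|
| Normal | 78.4% | 60.4% | 18 |
| Logistic | 82.4% | 70.0% | 12 |
| t, 5 df | 85.3% | 75.4% | 10 |
| Laplace | 86.0% | 82.1% | 4 |
| t, 3 df | 93.4% | 90.2% | 3 |
| Uniform | 72.4% | 38.9% | 34 |
| Exponential, skewed with the shift | 86.6% | 48.2% | 38 |
| Exponential, skewed against the shift | 83.2% | 83.7% | −1 (a gain) |

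In the two skewed rows the tests also target different location parameters: the median for the sign test, the pseudo-median for the signed-rank test. Those gaps are not pure efficiency losses.

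**5. Skewed raw values with a shift on the log scale.** This case arises if normality is judged on raw values. Assume lognormal values at both visits, log-SD 0.4 to 1.0, correlation 0.5 to 0.9, n = 20 and a standardized log-change of 0.667. The signed-rank test on raw changes then has 70 to 77% power and Friedman 60 to 62%, a loss of 10 to 16 points. The signed-rank test on log changes has about 77 to 79%.

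**The case against.** Four objections have force.

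- **Friedman is only an example.** The sentence introduces it with *such as* and also allows log transformation. A reader might infer that skewed cytokines, insulin or triglycerides must go through Friedman. The text does not say so: a log transformation followed by the paired t-test is open under the same sentence, and the signed-rank test is not excluded. What stands is that the one test named does not fit the two-visit outcomes.
- **Not every outcome has two occasions.** A reader might take "Data collection occurs at baseline and final visits" to cover everything. App-use and wearable series, and possibly the three 24 h recalls, can supply three or more occasions, and Friedman with pairwise comparisons could be right there. The article does not say which outcomes it is meant for.
- **No single power figure applies.** A reader might settle on a loss of 12 to 18 points. At n = 20 those are the logistic and normal cases, and normal changes would largely go to the t-test. Nor are all affected outcomes small: IPAQ is collected at all eight sites, with 20 + 15 + 52 + 20 + 15 + 15 + 25 + 20 = 182 required completers.
- **The signed-rank test has its own assumption.** Read as a test of location, it needs roughly symmetric changes; the sign test for the median does not. This is a real but small downside, eased by working on the log scale.

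It can also be said that matching each outcome to a test belongs in an analysis plan not shown here. That is fair for the detailed mapping, but it does not cover an example that is stated and does not suit the design.

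**Conclusion.** The mismatch is real and limited. For outcomes measured only at Day 0 and Day 90, Friedman with pairwise comparisons is the sign test with an empty follow-up step, while the paired t-test in the same paragraph fits. That conclusion is algebraic and needs no distributional assumption.

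The size of the harm does need one. At n = 20 and d = 0.667 it runs from practically nothing to more than 30 points, depending on the shape of the changes, so any figure quoted should carry its n, effect and shape. The documents do not support a general power loss, or a claim that the plan commits all skewed outcomes to an inefficient test.

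I rate it minor: the test is offered as an example, the outcomes are called mainly descriptive, and the sample size rests on the paired comparison of use. It is still worth correcting, since the same paragraph sets a significance level and uses tests of change to judge the effect on health outcomes.

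**What to change.** Replace the sentence in section 3 with one that separates the two cases:
- **Two-visit outcomes:** if the within-person changes are not approximately normal, use the Wilcoxon signed-rank test on those changes, taken on the log scale where the log transformation already allowed makes them more symmetric.
- **Three or more occasions** (such as app-usage series): keep Friedman with pairwise comparisons, and list the outcomes concerned.

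State that normality is judged on the within-person changes, which is what the paired t-test requires.

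The cost is a sentence or two of text. No extra data or participants are needed, and both tests are available in SPSS and R, the packages already named. The one price is the rough-symmetry assumption when the signed-rank result is read as a statement about location.

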## 4. Ethics

Compliance and Ethical Oversight: The research will be conducted in full compliance with the study protocol, good clinical practices, internal quality control systems, and the ethical guidelines set forth in the Declaration of Helsinki. The study will adhere to local regulations and legal requirements, with appropriate ethical approval obtained from relevant ethics committees in each participating country: the Balearic Islands Ethics Committee (CEIm-IB; reference: IB5752/25PI; 9 July 2025), by the Ethics Committee of University of Gastronomic Sciences, the Ethical Review Board of Eindhoven University of Technology (ERB-TU/e; ref. ERB2024BE40; 13 June 2024), the Ethics Committee of the University Bremen (ref. 2024-22; 10 September 2024), Ethics Committee of the Institute for Interdisciplinary Research of the University of Coimbra (CEIIIUC; ref. 35_ID1347; 9 September 2024), the Ethics Committee of the University of Evora (ref. 24099; 18 February 2025), the Ethics Committee of the University of Sofia, and the CITA’s Ethics Committee (CEISH; 27 November 2024).

Participant Benefits and Risks: Participants in the study will receive feedback on their health status, based on measurements previously explained. At the conclusion of the study, participants will have continued access to the HLRS mobile app features, at their own discretion and risk. The potential risks associated with this study are minimal. Aside from minor discomfort from peripheral blood draws, no invasive procedures will be carried out. Participants who experience significant medical issues, such as severe allergic reactions or high fever, will be withdrawn from the study. Likewise, individuals experiencing emotional or psychological distress will be advised to seek professional help and may be withdrawn if necessary. Given that the study includes a mobile application, there are inherent risks such as potential breaches of personal or health data security. However, these risks are considered minimal, and measures will be implemented to ensure the privacy and protection of participant information.

The safety reporting period for this study will extend from the initiation of the study until its conclusion. Any adverse events (AEs) related to the study will be monitored until they are resolved or until the study concludes, whichever occurs first. The definitions and management of adverse events are as follows:Adverse Event (AE): Any untoward medical occurrence in a participant related to study procedures (e.g., blood sampling). AEs may include any unfavorable or unintended symptoms or diseases, regardless of whether they are directly caused by the study procedures.Serious Adverse Event (SAE): A severe adverse event includes events that result in the following:Death;Life-threatening conditions;Requirement for inpatient hospitalization or prolonged hospitalization;Persistent or significant disability/incapacity;Congenital anomalies or birth defects. Serious events may also include medical occurrences that, based on medical judgment, could jeopardize the participant’s health and require intervention to prevent one of the aforementioned outcomes.

The intensity of AEs will be graded on a scale from mild to life-threatening, as follows:Grade 1 (Mild): Asymptomatic or mild symptoms, no intervention needed.Grade 2 (Moderate): Minimal intervention required, may limit daily activities.Grade 3 (Severe): Requires significant intervention, may limit self-care.Grade 4 (Life-threatening): Urgent intervention needed.Grade 5 (Death): Death related to the AE.

All serious adverse events must be reported immediately to the medical principal investigator within 24 h of occurrence, who will include these events in the annual report submitted to the local ethics committees. All project partners will secure an insurance policy in accordance with local regulations to provide coverage for any injuries or damage that may occur during the clinical study.

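### Safety withdrawal is from the whole study, so participants withdrawn before the final visit have no PHQ-9 or WHOQOL change score; where distress is the reason, the before-after result may be biased favourably

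*Protocol article*

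**What the plan says.** Section 4 (Ethics, participant benefits and risks) has two withdrawal rules. The medical one is mandatory: "Participants who experience significant medical issues, such as severe allergic reactions or high fever, will be withdrawn from the study". The psychological one is discretionary: "individuals experiencing emotional or psychological distress will be advised to seek professional help and may be withdrawn if necessary". Both concern the study as a whole; neither mentions stopping the app while staying in follow-up.

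Section 3 (Statistics) says what happens next:

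- "Participants who withdraw will be excluded from further analysis beyond their last available data"
- "No imputation will be performed for missing data"
- "replacements will be made as necessary, ensuring at least 20 participants complete the study"

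It closes with the claim "This method safeguards the integrity of the data and minimizes potential bias". Change over time is tested by paired t-tests, or by non-parametric methods such as the Friedman test where data are not normal.

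On timing, Section 2.6 states: "Data collection occurs at baseline and final visits". The final visit is Day 90 at most sites. Section 2.1 describes a single-arm design without a control group.

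On safety, Section 4 says that study-related adverse events "will be monitored until they are resolved or until the study concludes, whichever occurs first".

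**The concern.** Each rule is ordinary by itself. In combination they let the reason for leaving the study decide who is analysed. Distress is a ground for removal, and PHQ-9 and WHOQOL measure closely related things. A participant whose mood worsens enough to be withdrawn is therefore someone whose change score would probably have been poor, and that score is never obtained. Replacement restores the number of completers but not the missing kind of participant. With one arm, there is no comparator in which the same loss would occur.

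The pilot is meant to prepare a 12-month controlled study. An over-favourable picture of mood and quality of life would carry into the planning of that study. A later analysis plan could not repair this, because final questionnaires that were never requested cannot be recovered.

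**Working it through.** **The plan's own figure.** The only calculation in Section 3 is the sample size for app use: a difference of 20%, an SD of 30%, a significance level of 0.05 and 80% power. The two-sided normal approximation is (30 × (1.960 + 0.842) / 20)² = 17.66, so 18. The exact paired t-test needs 20 (power 80.7%). Allowing for 33% attrition, 20 / 0.67 = 29.9, so 30. The figures of 20 and 30 reproduce and are not in dispute. The plan gives no figure for bias from withdrawal.

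**Who loses a change score.**

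1. A participant is withdrawn from the study after baseline and before the final visit (Section 4).
2. Questionnaires are placed at those two visits (Section 2.6), so only the baseline value exists.
3. Nothing is imputed, and nothing after the last available data is used (Section 3).
4. A paired t-test needs both values, and so does the Friedman test. The participant drops out of the comparison.

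**Where it applies (Tables 1 and 4).**

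- PHQ-9 is marked Yes at six of eight sites. Target enrolment there is 30 + 30 + 101 + 30 + 30 + 30 = 251 of 351 (71.5%), and required completers are 20 + 15 + 52 + 15 + 15 + 20 = 137.
- WHOQOL is marked Yes at every site except CITA: 351 − 60 = 291 enrolled and 182 − 25 = 157 completers.

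**Size of the bias.** Let p be the proportion withdrawn and d the amount, in SDs of the change score, by which their mean change is worse than that of completers. The completers' mean then exceeds the full mean by p × d. The documents give neither p nor d, so all values below are assumptions.

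| p | d = 0 | d = 0.5 | d = 1 | d = 2 |
|---|---|---|---|---|
| 1% | 0 | 0.005 | 0.01 | 0.02 |
| 2% | 0 | 0.01 | 0.02 | 0.04 |
| 5% | 0 | 0.025 | 0.05 | 0.10 |
| 10% | 0 | 0.05 | 0.10 | 0.20 |

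As an extreme case, suppose exactly the worst p of normally distributed changes are removed. The bias is then φ(z) / (1 − p), where z is the 1 − p normal quantile: 0.027, 0.049, 0.109 and 0.195 SD for 1%, 2%, 5% and 10%.

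**Effect on the test.** Suppose there is no true change. The rejection rate of a two-sided 5% paired t-test comes from the noncentral t distribution with noncentrality bias × √n, treating the analysed changes as normal with SD 1:

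| Bias (SD) | n = 20 | n = 137 (PHQ-9 sites pooled) | n = 157 (WHOQOL sites pooled) |
|---|---|---|---|
| 0.05 | 5.5% | 9.0% | 9.6% |
| 0.10 | 7.1% | 21.3% | 23.8% |
| 0.20 | 13.6% | 64.2% | 70.2% |

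At one site of 20 the effect is slight unless the bias is at the top of the range. It grows when sites are pooled, because a fixed bias does not shrink with n.

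**The case against.** The strongest reply is that distress does not lead to automatic removal. The text advises professional help and allows withdrawal if needed. Only medical problems carry mandatory withdrawal, and the documents show no link between fever or allergy and PHQ-9 or WHOQOL. The number withdrawn for distress may be very small beside the 33% attrition already expected. This stands: the bias is possible, not established, and for the medical rule the consequence is mainly avoidable loss of data.

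A second reply is that a condensed article may leave withdrawal procedures to the full protocol. That would answer a complaint about missing detail. It does not answer this one, because the article itself states withdrawal from the study, exclusion, no imputation and replacement, and then claims that bias is minimized.

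Three stronger readings are tempting but unsupported:

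- **User-experience change is biased too.** The User Experience Questionnaire rates the platform, so it is not naturally a before-after score. Withdrawn participants would lack end-of-study ratings, with no established direction. The largest site (USG, 101 participants) is marked No for it.
- **The withdrawal and adverse-event rules contradict each other.** Safety monitoring can continue after withdrawal, and nothing restricts it to those still enrolled. The text simply does not say that it continues. For the same reason, it cannot be said that harm signals would be lost.
- **All outcomes are affected.** App use and wearable data accrue throughout, and Section 3 keeps data up to the last available point. The argument concerns the questionnaire change scores.

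**Conclusion.** The point holds as a cheap improvement. As written, a participant withdrawn between the two visits has no PHQ-9 or WHOQOL change. Where distress is the reason, the loss is related to the outcome, and the plausible direction is favourable. The size cannot be derived from the documents. It runs from 0 to 0.20 SD of the change score if 1% to 10% are withdrawn and their mean change is 0 to 2 SD worse than in completers. It could be close to zero if sites seldom use the discretionary rule. The claim in Section 3 that the method minimizes bias is not supported, since exclusion, no imputation and replacement do nothing to correct such a loss. The sample size of 20 completers and 30 recruited is unaffected.

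**What to change.** Reconcile Sections 3 and 4:

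- Make stopping the HLRS or a study procedure distinct from leaving the study.
- With consent, still ask those stopped for medical or psychological reasons to complete the final-visit questionnaires (Day 90 at most sites), and include these data in the before-after analyses.
- Report by site how many were stopped and why.
- Delete or qualify the statement that the method minimizes bias.
- State that adverse-event monitoring continues after withdrawal.

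When a participant should be stopped is left to the clinical leads; nothing here depends on changing those criteria.

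The cost is revised protocol and consent wording and a few extra contacts, some with people who have been unwell or distressed, so consent and burden need care. The questionnaires already run through REDCap, so no new instrument is needed. The results may look less favourable.

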## 5. Data Handling and Storage

Data will be handled in compliance with the GDPR. All participant data will be pseudonymized, ensuring that identifying information is securely stored separately from other data. The mapping between participant names and reference codes will be kept in a separate, secure location to maintain confidentiality. Data will be stored according to local regulations, with appropriate measures to protect it from unauthorized access, loss, or misuse, and will then be kept for an additional five years for future research purposes, in accordance with applicable legal and ethical guidelines. Participants will have the right to access, correct, or restrict the processing of their data, as well as the right to request the deletion of their data or samples, within 10 years after the study concludes. Cross-border data transfer agreements have been signed among partners to build a common database.

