Actigraph Accelerometers	Participants will be required to wear an ActiGraph accelerometer (ActiGraph wGT3X-B; ActiGraph LLC, Pensacola, FL, USA) continuously for nine consecutive days to objectively assess their physical activity levels and sedentary behavior. This device will provide detailed data on movement patterns, energy expenditure, and sleep–wake cycles, allowing for a comprehensive analysis of participants’ activity and rest periods. To ensure data accuracy, participants will be instructed on proper device placement and usage.
Calendar Web Application	Developed by EU HealthyW8 partner VirTech (Bulgaria), this application enables the study leader to schedule local events and inform participants. The event data is securely stored on servers at LIST, Luxembourg.
REDCap (Research Electronic Data Capture), VanDerBilt University (USA)	Used for completing intervention questionnaires. Additional information can be found at the following website: https://project-redcap.org/. The event data is securely stored on servers at LIST, Luxembourg.

**Table 3 jpm-15-00625-t003:** Tools used by each participating country in the young adults’ pilot study.

Country, Partner	Bulgaria, RCNE	Germany, BIPS/DFKI	Italy, USG	Netherlands, TU/e	Portugal, UC	Portugal, UEV	Spain, CITA	Spain, IDISBA
Length of intervention (months)	3	3	1.5	1–2	3	3	3	3
Length of run-in time	6	6	6	1	2	2	2	2
Gamebus	Yes	Yes	Yes	Yes	Yes	Yes	Yes	Yes
Nutrida	Yes	Yes	Yes	Yes	Yes	Yes	Yes	Yes
Wearable	Garmin	Samsung	Garmin	Samsung	Samsung	Garmin	Garmin	Garmin
Experiencer	No	No	No	Yes	Yes	No	No	No
Accelerometer	Yes	Yes	No	No	No	Yes	No	Yes
Calendar	Yes	Yes	Yes	No	No	Yes	Yes	Yes
Questionnaires	Yes	Yes	Yes	Yes	Yes	Yes	Yes	Yes
Biological samples and measures	Yes	No	No	No	No	Yes	No	Yes

Abbreviations: RCNE: Regional Cluster North-East; BIPS/DFKI: Leibniz-Institut fur Praventionsforschung und Epidemiologia-BIPS GmbH/Deutsches Forschungzentrum fur Kunstliche Intelligenz GmbH; USG: Universitá Degli Studi di Scienze Gastronomiche; TU/e: Eindhoven University of Technology; UC: Universidade de Coimbra; UEV: Universidade de Évora; CITA: Centro de Investigación y Tecnología Agroalimentaria de Aragón; IDISBA: Fundació Institut d’Investigació Sanitària de les Illes Balears.

**Table 4 jpm-15-00625-t004:** Measures included in pilot studies of each team.

Marker Class	Marker	Bulgaria, RCNE	Germany, BIPS/DFKI	Italy, USG	Netherlands, TU/e	Portugal, UC	Portugal, UEV	Spain, CITA	Spain, IDISBA

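### Study follow-up of a related serious adverse event stops when the study ends, even if the event is still open

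*Protocol article*

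**What the plan says.** All the relevant text on adverse events is in section 4 (Ethics) of the protocol article.

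- **Reporting window.** Safety reporting runs from the start of the study to its conclusion. No later window is given.
- **Stopping rule.** "Any adverse events (AEs) related to the study will be monitored until they are resolved or until the study concludes, whichever occurs first".
- **What counts as serious.** The SAE definition lists death, life-threatening conditions, "Requirement for inpatient hospitalization or prolonged hospitalization", lasting disability and congenital anomaly.
- **SAE handling.** "All serious adverse events must be reported immediately to the medical principal investigator within 24 h of occurrence". The onward step is an entry by that investigator in a yearly report to the local ethics committees.
- **Expected risk.** "The potential risks associated with this study are minimal".

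Section 4 also requires each partner to hold insurance for injury or damage during the study. That sentence concerns cover for harm and says nothing about follow-up.

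**The concern.** Ending follow-up of a minor event at study close is reasonable. For a serious event the end of follow-up should depend on the participant's condition. Here the earlier of two dates decides, and one of them is administrative. If a related SAE is unresolved on that date, study monitoring stops.

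What is at stake is the completeness of the safety record. The ethics committees would know that the event happened but might not learn how it ended. The gap would fall on events that do not resolve quickly, whose outcome matters most. The efficacy and usage analyses are not touched.

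**Working it through.** This is a check of text. The plan gives no figure to reproduce on this point.

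**Step 1. Does the rule cover serious events?** Yes. It applies to any related adverse event, and section 4 defines an SAE as a severe form of adverse event.

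**Step 2. Does an SAE-specific provision override it?** There are two such provisions:

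| Provision | What it requires | Follows the event to outcome? |
|---|---|---|
| Report to the medical principal investigator | Within 24 h of occurrence | Not required |
| Annual report to the ethics committees | The event is included | Not required; content and timing are not stated |

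**Step 3. Does anything elsewhere extend follow-up?** No. The rest of the article contains no SAE exception and no post-study window. The general commitment to good clinical practice and local regulations in section 4 sets no follow-up duration, and the same sentence commits sites to comply with the protocol.

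**Step 4. Can a listed SAE outlast the study?** Yes. Section 2.6 gives a study length of 90 days. A hospital stay can run past the closing date, and lasting disability or a congenital anomaly may not resolve within that time. Section 2.6 also repeats assessments at the Day 90 visit. Where blood sampling is repeated then, it falls on the participant's last study day.

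**Step 5. Does the meaning of study conclusion matter?** The article does not define it.

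- If it means the participant's own last visit, an event arising at that visit gets almost no monitoring.
- If it means the end of the whole trial, early enrollees are followed longer, but an SAE still open on the closing date is dropped.

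The reading changes how often the gap could arise. It does not close the gap.

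**Step 6. Size.** No adverse event rate is given, so no share of affected events can be computed. For context only, blood sampling is the one source of adverse events that the AE definition names as an example. The number of targeted participants at sampling sites can be counted from the tables:

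- All sites (Table 1): 30 + 30 + 101 + 40 + 30 + 30 + 60 + 30 = 351.
- Table 3, row "Biological samples and measures": RCNE 30 + UEV 30 + IDISBA 30 = 90.
- Table 4, blood markers: UC 30 + UEV 30 + IDISBA 30 = 90.
- Either list: 90/351 = 25.6%.
- The lists name partly different sites and agree on 90 only because each of these sites targets 30. Sites in either list: 4 × 30 = 120, and 120/351 = 34.2%. Sites in both: 2 × 30 = 60, and 60/351 = 17.1%.

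These are participants who may be sampled, not events. The AE definition is also not limited to sampling. The conclusion does not rest on these figures.

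**The case against.** The strongest reply is that this is a condensed article, that SAE follow-up is normally detailed in the full protocol, and that section 4 already promises good clinical practice and compliance with local rules. If the article were silent, that would settle the matter. It is not silent: it states when monitoring ends, and a site that follows the text would stop. A general clause with no follow-up duration does not correct a specific instruction.

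A second reply is that the annual ethics report may be written after the study closes and may state the outcome. That is possible, since its content and timing are not given. For this reason the claim is only that the outcome may be lost.

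A third reply is that the practical effect is close to nil. This is an app and wearable pilot in adults aged 18–25, and the gap needs an event that is related, serious and still open at conclusion. Nothing in the article says that clinical care stops, and sites may follow such events anyway. This stands, and it is why the point is minor. It does not justify keeping a rule that permits an open related SAE to be dropped.

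**Conclusion.** The concern holds and is minor. As written, study monitoring of a related SAE ends at study conclusion even if the event is unresolved, and no other provision in the article requires its outcome to be recorded. Few events are likely to be affected, and the number cannot be estimated from the document. The event itself would still be reported, and no efficacy result changes.

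The conclusion assumes that sites follow the stated rule and that no fuller document, not available here, overrides it. It does not depend on how study conclusion is defined or on any event rate.

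**What to change.** Keep the present rule for non-serious events and add one sentence to section 4:

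*Related SAEs will be followed until resolved or stable and their outcome recorded, even if this falls after the study concludes.*

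The cost is an occasional extra contact with a participant whose related SAE is still open. Contact looks feasible. Section 5 (Data Handling and Storage) states that "The mapping between participant names and reference codes will be kept in a separate, secure location to maintain confidentiality", and it gives participants "the right to request the deletion of their data or samples, within 10 years after the study concludes", which suggests that records can still be linked to individuals after the study. Section 5 gives no retention period for the mapping, so sites should confirm that it is kept at least until any open SAE is closed. Section 2.1 presents this pilot as the basis for a 12-month controlled study, so correcting the sentence now also keeps it from being carried forward.
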